#### Sample size

Previous studies of the interventions for patients with mild Alzheimer’s disease included in our multicomponent treatment programme found small-to-medium effect sizes for depression outcomes (*d* = 0.4 to 0.6, corresponding to *f* = 0.2 to 0.3) [12, 15, 21, 43]. We base our sample size calculation on the assumption of a small-to-medium effect size for depression as measured using the Geriatric Depression Scale (*d* = 0.5, *f* = 0.25). The sample size was calculated using G*Power 3.1.0 software [55]. Assuming *α* = 0.05 and a test power 1 − β = 0.80, a total sample size of *n* = 44 is required to test condition × time interactions in an analysis of variance (ANOVA) with repeated measurements (*r* = 0.3). Since previous studies on CBT-based psychotherapy for caregivers of people with dementia found medium [21] or large [23] effect sizes on mood measures (depression, anxiety), this sample size should also be sufficient to find an effect of the intervention on caregiver’s mood. We assume a rather conservative rate of loss of 60 % from the screening of eligibility to the enrolment of subjects. Thus, we propose to start with approximately 120 patients and caregivers at the screening, which we expect to reduce to 50 at enrolment. A drop-out rate of approximately 10 % would lead to *n* = 44.

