### Randomization

After providing informed consent and receiving a baseline assessment, the participating couples will be individually randomized. The allocation ratio for randomization into either the intervention or control condition is 1:1. The randomization will be performed by a computer algorithm independently operated by the Clinical Trial Centre of the University Hospital Zurich. The results of the randomization will be sent to the study nurse, who will telephone the participant and the caregiver to explain the next steps.

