### Methods against biases

The proposed study employs several methods to avoid biases:*Selection bias* The randomization procedure is the gold standard to avoid this bias.*Detection bias* The baseline assessment is made before randomization to avoid this bias. In addition, the therapists will not collect any outcome data t post-test or follow-up assessments. This will be done by blinded members of the research team (single-blinded trial). Research assistants and therapists will be instructed during their training on the importance of maintaining the blinded status. The participants will be asked not to comment at post-test or follow-up assessments on the nature of their involvement in the study.*Performance bias (intervention fidelity)* To confirm that the intervention has been delivered and received as intended, a standardization procedure (manual, extensive training and session documentation, including an adherence checklist and supervision) has been established.*Attrition bias* Statistical analysis will include techniques to minimize a possible attrition bias, i.e., intention-to-treat analysis and imputing missing data. In the case of dropping out, it is intended to continue data collection whenever possible.

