### Statistical analysis

Several analytical strategies are planned, to test the efficacy of the intervention. First, ANOVAs will be conducted to compare the mean outcome in depressive symptoms. The sex, age, caregiver’s relationship (spouse, child, close friend) and severity of cognitive impairment and depressive symptoms at baseline will be considered covariates. Second, individual growth curves will be analyzed, i.e., the rates and shapes of changes will be examined and individual growth curves will be compared, to investigate the differences. Third, multivariate analyses will be used to test the effect of the intervention with regard to the secondary and caregiver outcome measures. In this way, correlations between the outcome measures can be considered. Post-hoc analyses will be performed following a significant overall effect.

A complete dataset will be available if all four tests (pre-test, post-test and follow-ups 1 and 2) have been completed. Dropping out can occur if a participant (1) does not complete the pre-test, (2) decides, after information or randomization, against participation, or (3) starts with the treatment, but discontinues it. If fewer than 20 % of the items of one’s self-report instrument are missing, the missing values are imputed using the mean of the scale for this participant. If the whole scale is missing, the value will be imputed using the expectation-maximization algorithm.

The data and all appropriate documentation will be stored for a minimum of 10 years after the completion of the study, including the follow-up period.

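### Filling a missing whole scale once by expectation-maximization gives standard errors that are too small if condition is in the imputation model, or a diluted effect if it is not; the protocol does not say which

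*Protocol article*

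**What the plan says.** The Statistical analysis section of the protocol article gives two rules for missing data. When fewer than 20% of the items of a self-report instrument are missing, they are filled with the participant's own mean on that scale. For a scale that is missing altogether: "If the whole scale is missing, the value will be imputed using the expectation-maximization algorithm".

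The Methods against biases section makes this part of the defence against attrition: "Statistical analysis will include techniques to minimize a possible attrition bias, i.e., intention-to-treat analysis and imputing missing data". The first analysis listed is an ANOVA of depressive symptoms with covariates that include baseline depression. Individual growth curves come second.

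Neither section mentions multiple imputation, an added residual or a variance correction, and neither says which variables enter the EM model. The Sample size section supplies the expected loss: 50 enrolled, and "A drop-out rate of approximately 10 % would lead to *n* = 44".

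**The concern.** A value from EM is a prediction. If it is entered once and analysed like a measured score, the ANOVA treats the patient as fully observed and the prediction as free of error.

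The prediction is weak here. With the planning correlation of 0.3, a baseline score explains 0.3² = 9% of the variance of a later score. For a patient with only a baseline score, the fill therefore leaves out about 91% of the real variability.

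What follows depends on one modelling choice that the article leaves open:

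- **Condition in the EM model, or EM run by arm.** Filled values lie on each arm's own fitted line. The estimate is unbiased if dropout is at random, but its standard error is too small.
- **Condition not in the EM model.** Filled values are drawn towards a line common to both arms, and the estimated difference shrinks.

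The result at stake is the treatment comparison on the primary outcome in a trial of 50 patients, where about six filled patients are enough to matter.

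**Working it through.** **Inputs from the protocol article.** Sample size section: α = 0.05, power 0.80, d = 0.5 (f = 0.25), r = 0.3, 44 required, 50 enrolled. Randomization section: 1:1. Statistical analysis section: four assessments.

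**The plan's own figures.** For a within-between interaction, λ = f²·N·m/(1 − r), with m − 1 and (N − 2)(m − 1) degrees of freedom. With m = 2 and N = 44, λ = 0.0625 × 44 × 2/0.7 = 7.86 and power is 78.2%; 80% needs N = 46. The stated 44 is thus reproduced to within two patients, taking m = 2 (the article does not state m). The loss from 50 to 44 is 6/50 = 12%; the article's rounded figure is 10%.

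**Condition in the EM model, closed form.** Let p be the fraction missing. Filled points on the fitted line add nothing to the residual sum of squares, yet the error variance is divided by about N instead of N(1 − p). The standard error then also uses N instead of N(1 − p). Reported variance is about (1 − p)² of the true variance, so

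- SE ratio (reported/true) ≈ 1 − p
- type I error ≈ 2[1 − Φ(1.96(1 − p))]

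p = 0.10: ratio 0.90, type I error 7.8%. p = 0.12: ratio 0.88, type I error 8.5%.

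**Condition omitted, closed form.** Filled patients contribute no difference between arms, so the estimate is about (1 − p) × d. At p = 0.12 this is 0.88 × 0.50 = 0.44. The estimate's sampling SD shrinks by the same factor, so the test keeps its level.

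**Simulation check.** 50 patients, 1:1, normal data, four visits with common correlation 0.3, dropouts chosen at random and missing every post-baseline visit, conditional-mean EM fill, baseline as the only covariate, 3,000 to 4,000 runs per setting (Monte Carlo error about 0.4 to 0.5 percentage points). Type I error at nominal 5%:

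| Method | Missing | Post-test ANCOVA | Two-visit interaction | Four-visit interaction | SE ratio (ANCOVA) |
|---|---|---|---|---|---|
| EM, condition in | 10% | 7.8% | 7.2% | 8.9% | 0.89 |
| EM, condition in | 12% | 8.4% to 9.2% | 7.7% | 9.9% | 0.86 to 0.87 |
| EM, condition omitted | 10% | 5.8% | 5.1% | 5.2% | 0.99 |
| EM, condition omitted | 12% | 4.3% to 5.0% | 4.4% | 5.0% | 1.00 to 1.03 |
| Multiple imputation, condition in | 12% | 4.7% | not run | not run | 1.01 |
| Observed cases only | 12% | 5.9% | 5.5% | 5.6% | 0.97 |

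With a true effect of 0.50 SD and 12% missing, the mean post-test estimate was 0.50 with condition in the EM model, 0.44 with condition omitted, and 0.50 under multiple imputation. Power was 49.2%, 38.7% and 38.0% respectively. The apparent gain in the first case comes from the understated standard error. The similar power in the other two shows that omitting condition distorts the estimate, not the test.

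A separate simulation with monotone dropout gave 7.9% with condition in the model and an estimate of about 0.45 with condition omitted, both at 12% missing.

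**The case against.** **The article is condensed.** It does not say that the fill is made once, that it is the conditional mean, or that it is analysed as observed. A full analysis plan may settle these points, and silence on them is no fault. But the article does name a specific method, and a single fill is the natural reading of it. Adding one random residual would not repair the standard error when condition is in the model. For a comparison of means the true variance is then about [1/(1 − p) + p] times the reported one. At p = 0.12 that is 1.136 + 0.12 = 1.256, an SE ratio of about 0.89 and type I error of about 8%.

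**Dropout is not the same as a missing score.** This stands. The article counts as dropouts people who discontinue treatment, yet it intends to go on collecting their data where possible. Under Consent, participants given an alternative treatment stay in follow-up and analysis. It also counts people who do not complete the pre-test, who would never be randomised because randomisation follows baseline. Missing scores may therefore be fewer than 12%. If 5% were missing (an illustration, not a figure from the article), type I error with condition in the model would be about 6.3%.

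**Growth curves may not need the fill.** They can use incomplete data by likelihood. The article does not say whether they will, and that would not repair the ANOVA listed first.

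**A stronger reading is tempting.** A reader might infer that the rule necessarily raises type I error above 5%. The article does not support this: with condition omitted from EM, type I error stayed between 4.3% and 5.8% in every setting run, including 5.2% with all dropout in one arm. A reader might also quote the much larger errors that follow from heavy loss at the 12-month follow-up, but the article gives no such missing rates.

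**Conclusion.** The stated rule is deficient, and its consequence is one of two.

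- **Condition in the EM model, or EM by arm:** reported standard errors are about 0.86 to 0.89 of their true size, and type I error is roughly 7% to 10% at 10% to 12% missing.
- **Condition omitted:** type I error is near 5%, but a true 0.50 SD effect is reported as about 0.44 to 0.45 SD at 12% missing.

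The article does not show which applies, so inflated type I error should be stated as conditional.

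These sizes assume that every planned dropout is a missing score, that dropout is at random, normal data, a common correlation of 0.3, a conditional-mean fill without residual, and baseline as the only covariate. The direction in each case does not depend on the exact rate. Severity: should-fix.

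**What to change.** Replace the sentence on whole scales with one of the following:

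1. Multiple imputation with condition, baseline, the stated covariates and all visits in the model, the planned ANOVA run on each completed dataset and the results combined by Rubin's rules. In the simulation (condition and baseline in the model) this gave type I error of 4.7% and 4.5% at 12% and 20% missing (the 20% is an assumed rate), with SE ratios of 1.01 and 1.02.
2. A likelihood-based mixed model on all observed visits of all randomised patients, without filling in whole scales.

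The growth-curve analysis can likewise use the observed visits directly. Keep the person-mean rule for fewer than 20% of items.

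The cost is analysis wording only; no patients or visits are added. Compared with a single fill with condition in the model, confidence intervals widen, by a factor of about 1/0.88 = 1.14 at 12% missing, which restores their proper width. Compared with a fill without condition, the estimate also moves back to its undiluted size.

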### Regulatory issues

#### Ethical approval

Ethical approval has been obtained through the Swiss Ethics Committee in the Canton of Zurich (reference number 2009–0078/3). The study will be conducted in accordance with the principles enunciated in the current Declaration of Helsinki, the Guidelines of Good Clinical Practice issued by the International Conference on Harmonisation and the Swiss regulatory authority’s requirements. Participation in the study is voluntary. There are no negative consequences for non-participation or dropping out. Patients who decline to participate or drop out receive medical and psychosocial care as usual. The participants are informed of the study conditions in detail (verbally and in writing) and specific questions can be discussed. Ethical challenges may arise as a result of randomization. However, the control conditions are active treatment conditions, so participants in any study condition will benefit if they enrol in the study.

#### Consent

Consent to enter the study will be sought from each participant only after a full explanation has been given, an information leaflet offered and time allowed for consideration. Signatures to indicate participants’ consent will be obtained. The right of the participant to refuse to participate without giving reasons will be respected. After participants have entered the study, clinicians remain free to provide an alternative treatment to that specified in the protocol at any stage, if they consider it to be in the participant’s best interest, but the reasons for doing so will be recorded. In these cases, the participants remain within the study for the purposes of follow-up and data analysis. All participants are free to withdraw at any time from the protocol treatment without giving reasons and without prejudicing further treatment.

#### Confidentiality

The principal investigator will preserve the confidentiality of the participants in the study and is registered under the Data Protection Act.

#### Insurance

Insurance coverage will be provided by Zurich Versicherungsgesellschaft, Zurich, Switzerland (policy number 9.730.682), for a maximum of 3,000,000 Swiss francs.

#### Audits

The study may be subject to inspection and audit by regulatory bodies, to ensure adherence to the Guidelines of Good Clinical Practice, national law and regulatory requirements. The auditor will be independent from the investigators and the sponsor.

#### Adverse events

An adverse event is any untoward medical or psychological occurrence in a study subject, e.g., worsening of symptoms. A serious adverse event is any untoward medical or psychological occurrence or effect that results in death, is life-threatening (this refers to an event in which the subject was at risk of death at the time of the event but does not refer to an event which hypothetically might have caused death had it been more severe), requires hospitalization or prolongation of existing inpatients’ hospitalization, or results in persistent or significant disability or incapacity. Medical or psychological judgement will be exercised in deciding whether an adverse event is serious. Important adverse events that are not immediately life-threatening or do not result in death or hospitalization but may jeopardize the subject or may require intervention to prevent one of the other outcomes listed in the serious adverse event definition will also be considered serious.

All adverse events will be reported. Depending on the nature of the event, the following reporting procedures will be followed:*Non-serious adverse events* All such events, whether expected or not, will be recorded.*Serious adverse events* A serious adverse event form will be completed and faxed to the principal investigator within 24 hours. However, hospitalizations for an elective treatment of a pre-existing condition does not need to be reported as a serious adverse event.

The principal investigator will assess whether the event is:*‘related’*, i.e. results from the administration of any of the research procedures;*‘unexpected’*, i.e. is not listed in the protocol as an expected occurrence.

Reports of suspected related and unexpected serious adverse events will be submitted to the ethics committee within 15 days (or within 7 days for fatal or life-threatening serious adverse events) of an investigator becoming aware of the event.

## Discussion

This trial is a CBT-based, multicomponent treatment implemented with state-of-the-art randomized controlled trial methodology. A recent report on national dementia strategies concludes that any national dementia plan should include, among other things, the goals of improving early diagnosis and treatment, of improving support to the person with dementia living at home, as well as to the caregiver, and of improving training for healthcare professionals [86]. This trial has the potential to establish an empirically based psychological treatment for non-cognitive symptoms that reduce the quality of life of the person with dementia and the caregiver. The treatment manual will be published and training workshops will be offered, so that the information can be widely spread among healthcare professionals. This CBT-based treatment is potentially a side-effect-free alternative to medication for neuropsychiatric symptoms. In the case of affective and behavioural symptoms, there is a strong case for psychosocial intervention prior to resorting to medication [87]. Furthermore, health care costs might be reduced through decreased use of medication and delayed nursing home placement.

This treatment approach focuses not only on the person with dementia, but also on the caregiver and on the dyad. It will empower the caregiver to take part in the treatment and, at the same time, will improve the caregiver’s own mental health and well-being.

Treatment guidelines list a larger number of psychosocial interventions for dementia. However, empirical evidence for many of the approaches is lacking, as recent reviews conclude [9–11]. This trial, with state-of-the-art methodology, has the potential to provide evidence for future guidelines for the psychological treatment of people with dementia and their caregivers.

### Trial status

The trial is in the recruiting phase at the time of manuscript submission.

## Abbreviations

ANOVA: analysis of variance
CBT: cognitive behavioural therapy
CBTAC: Cognitive behavioural treatment for mild Alzheimer’s patients and their caregivers
CERAD: Consortium to Establish a Registry for Alzheimer’s Disease
CONSORT: Consolidated Standards of Reporting Trials
NINCDS–ADRDA: National Institute of Neurological and Communicative Disorders and Stroke/Alzheimer’s Disease and Related Disorders Association
